### 3.1. PRIMARY OBJECTIVE AND OUTCOME

- The primary objective is to prove non-inferiority of immunogenicity of a reduced BNT162b2 vaccine dose (20µg) versus the reference vaccine dose (30µg).
- The primary outcome is the geometric mean titer (GMT) of binding (IgG) antibodies specific to the receptor binding domain (RBD) of SARS-CoV-2 at four weeks after the second dose.

Data from the literature and from our own PICOV-VAC data indicate strong correlation between titers of RBD binding antibodies and neutralizing antibodies. As methods to measure RBD binding antibodies can be implemented more rapidly than neutralizing antibody assays, we consider that RBD binding antibodies are a good surrogate for neutralizing antibodies and can therefore be used as a primary endpoint for this study.

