## Sample size

The primary analysis is a non-inferiority comparison at 28 days after the second dose, for the GMT of antibodies binding to the RBD of SARS-CoV-2, comparing the reference dose (30µg BNT162b2) with the reduced dose (20µg BNT162b2).

Currently available data from published and ongoing COVID-19 vaccination trials indicate that:

- RBD-specific antibody titers (GMT, arbitrary units) 28 days after the second dose of BNT162b2 equals 2125. The standard deviation on the log scale (base 10) is 0.27 (PICOV-VAC trial).

The following assumptions are made in the sample size calculations:

- The non-inferiority margin is -0.15 absolute difference of GMT on log scale (base 10), between a reduced dose and regular dose vaccine schedule.
- The standard deviation of GMT on the log10 scale is 0.27 for BNT162b2, based on the currently available data.
- The true difference of GMT on log10 scale is 0.
- A two-sided 2.5% family-wise error rate (at cohort level).

Based on these assumptions, the comparison between both doses will need a minimum of 50 participants (infection naïve) per group to achieve 90% power. In order to be able to better evaluate reactogenicity however, we aim for a larger sample size.

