## Trial randomization

Subject randomization will be done using statistical software (RStudio). The system will randomly allocate the 150 participants across both study arms (20µg and 30µg) irrespective of their previous SARS-CoV-2 infection status. The recruitment and randomization process will aim to have a balanced representation of age and gender across the study arms. Therefore stratified randomization will be used based on age and gender.

In addition, 20 participants will be randomly selected per study arm (40 in total) from which extra (heparinized) blood will be collected for in-depth cellular immunogenicity analyses (see table 1). This random selection will be done using the same statistical software (RStudio).

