### Statistical analyses

The analysis described here will be coordinated by the Sponsor. Any later analyses on the linked data will also be conducted by the Sponsor.

All of the participants who meet the eligibility criteria will be included in the main analysis. Descriptive analyses will be used to report participant characteristics. The level of antibody titers in each of the study arms will be analyzed with the Kruskal-Wallis test, while participant demographics (e.g. age, gender) will be taken into account (confounders). Furthermore, risk factors and correlations with antibody detectability will be evaluated. P-values below 0.05 will be considered statistically significant.

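### The only test named for antibody titres, Kruskal-Wallis at p<0.05, contradicts the protocol's own non-inferiority comparison against -0.15 log10 and cannot deliver it

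*Protocol*

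**What the plan says.** Three parts of the protocol bear on the primary comparison.

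- **Section 3.1** sets the aim: "The primary objective is to prove non-inferiority of immunogenicity" of 20 µg against 30 µg. It also sets the endpoint: "The primary outcome is the geometric mean titer (GMT) of binding (IgG) antibodies specific to the receptor binding domain (RBD" at four weeks after the second dose.
- **Sample size** repeats the framing: "The primary analysis is a non-inferiority comparison at 28 days after the second dose". It fixes the margin, "The non-inferiority margin is -0.15 absolute difference of GMT on log scale (base 10", together with an SD of 0.27 log10, a true difference of 0 and a two-sided 2.5% error rate. From these it derives a minimum of 50 infection-naïve participants per group.
- **Statistical analyses** puts all eligible participants in the main analysis. It then says: "The level of antibody titers in each of the study arms will be analyzed with the Kruskal-Wallis test". The same sentence says that demographics such as age and gender will be accounted for as confounders, and the paragraph sets significance at p<0.05. It gives no margin, GMT ratio, confidence interval or non-inferiority rule.

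Two other places matter. Trial randomization says: "Therefore stratified randomization will be used based on age and gender". Discontinuation criteria and Blinding/unblinding make unblinding and the offer of a further dose depend on whether the reduced dose is found inferior.

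**The concern.** The analysis section names a method for a different question from the one the trial asks. Kruskal-Wallis with two arms is the two-sided rank-sum test of equal distributions. A non-significant result may only mean that the trial was too small to see a difference, and a significant one does not show that the difference exceeds the margin. The test works on ranks, while the endpoint and margin are set on mean log10 titre, so its output cannot be set against -0.15.

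An analyst who follows the Statistical analyses section has no valid route from the named test to the primary conclusion. An analyst who follows the Sample size section must set the named test aside. The primary result decides whether participants are unblinded and offered a further dose, so the choice should not be left to whoever runs the interim analysis.

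**Working it through.** **Inputs, all from the Sample size section unless noted.** Margin -0.15 log10; SD 0.27; true difference 0; two-sided error 2.5%; 50 naïve per group. Section 3 gives 150 participants split equally, so 75 per arm, of whom up to 25 may be previously infected. Statistical analyses gives p<0.05.

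**1. The plan's own sample size.** Per group, n = 2 × SD² × (z₁₋α + z₁₋β)² / margin². Here 2 × 0.0729 / 0.0225 = 6.48.

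| One-sided α | Power | Calculation | n per group |
|---|---|---|---|
| 0.0125 (two-sided 2.5% taken literally) | 90% | 6.48 × (2.241 + 1.282)² | 81 |
| 0.025 | 90% | 6.48 × (1.960 + 1.282)² | 69 |
| 0.025 | 80% | 6.48 × (1.960 + 0.842)² | 51 |

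The stated 50 at 90% power is not reproduced; the nearest match is one-sided 0.025 at 80% power. That is a separate matter. What counts here is that the trial was sized for a difference in mean log10 titre judged against a margin, and Kruskal-Wallis does not make that comparison.

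**2. The margin as a ratio.** 10^(-0.15) = 0.708.

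**3. One illustrative result.** With 50 per arm the standard error of the mean difference is 0.27 × √(2/50) = 0.054. Suppose the observed difference is -0.10.

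- Test of no difference (normal approximation): z = -0.10 / 0.054 = -1.85, two-sided p about 0.06, not significant.
- Margin rule: lower 95% limit = -0.10 - 1.96 × 0.054 = -0.206, below -0.15, so non-inferiority is not shown.

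The same data give a non-significant test and a failed non-inferiority comparison.

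**4. How often a non-significant result occurs at the margin.** Trials were simulated with normal log10 titres, SD 0.27 in both arms and a true difference of -0.15.

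| | 50 per arm | 75 per arm |
|---|---|---|
| Kruskal-Wallis p≥0.05 | about 23% | 9% |
| Lower limit of 95% CI above -0.15 | 2.4% | 2.5% |
| Lower limit of 97.5% CI above -0.15 | 1.2% | 1.3% |

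Runs of 4,000 and 20,000 trials gave 23.1% and 23.8% at 50 per arm, and 8.7% and 9.2% at 75 per arm. As a rough analytic check, the rank test has efficiency 3/π relative to the t-test. So 50 per arm acts like 47.7, the standard error is 0.0553, and Φ(1.96 - 0.15/0.0553) = Φ(-0.75), or about 23%.

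At a true difference of -0.10 the test is non-significant in 57% of trials (50 per arm) and 41% (75 per arm). The 95% margin rule passes only 15% and 20% of trials there.

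**5. The opposite conflict.** A significantly lower 20 µg titre together with a met margin (95% CI) occurred in fewer than 0.2% of simulated trials in every setting. At these sample sizes the practical risk is therefore wrongly passing the reduced dose.

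**6. Error rate.** Sample size uses two-sided 2.5% and Statistical analyses uses 0.05. The two sections imply different confidence levels for the same primary comparison.

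**The case against.** The strongest reply is that the Statistical analyses section never calls Kruskal-Wallis the primary analysis. The Sample size section does name the primary analysis, with its margin, scale and time point. The Kruskal-Wallis sentence gives no time point and could describe a general comparison of titres, including the secondary visits. The estimator, interval and covariates are often left to a statistical analysis plan, which is not at hand.

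Much of this stands, and it limits the point in three ways:

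- A reader might infer that the protocol's declared primary analysis is Kruskal-Wallis. The documents do not say so. The defect is that two sections disagree.
- A reader might infer that the trial will declare non-inferiority when p≥0.05. No section states that rule, and the sections on unblinding and the further dose mention neither the test nor a p-value. The 23% and 9% are therefore conditional.
- A reader might infer that adjustment for age and gender has been made impossible. Plain Kruskal-Wallis takes no covariates, but the wording leaves room for a stratified rank test or a separate adjusted analysis. The text is vague on this rather than unworkable.

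The reply does not remove the core. Kruskal-Wallis is the only test named for titres, it sits in the main-analysis paragraph, and the primary endpoint is a titre that the sentence does not exempt. This is a wrongly named method, not a missing detail. An analysis plan could add the right analysis, but the contradiction would remain in the protocol.

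**Conclusion.** The point holds as an internal contradiction. Section 3.1 and Sample size require a margin-based comparison of GMTs, and Statistical analyses names a test of no difference that cannot provide it. This needs correcting before the primary analysis is run.

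The conclusion that the named test cannot show non-inferiority follows from what the test is and needs no simulation. The size does rest on assumptions. If non-significance were taken as non-inferiority, the false pass rate at the margin would be about 23% (50 per arm) or 9% (75 per arm) instead of 1.25% to 2.5%. That assumes normal log10 titres, complete data and SD 0.27 for everyone. The 75-per-arm figure applies that SD to previously infected participants too, whose spread may be larger and was not modelled.

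**What to change.** In Statistical analyses, state the primary analysis as follows:

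- **Model:** linear model of log10 anti-RBD IgG at four weeks after dose 2, with arm and the randomisation factors age and gender.
- **Population:** the infection-naïve participants on whom the Sample size section bases its calculation. Reconcile this with the present statement that all eligible participants enter the main analysis. Add previous-infection status, already recorded at baseline, as a term in any analysis that includes infected participants.
- **Report and rule:** the 20 µg minus 30 µg difference and the GMR with confidence interval. Declare non-inferiority only if the lower limit exceeds -0.15 (GMR 0.708).
- **Level:** one confidence level in both Sample size and Statistical analyses, namely 97.5% two-sided if the 2.5% there is meant literally.
- **Kruskal-Wallis:** supportive at most.

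The cost is a protocol amendment under section 7.7, with sponsor approval and ethics committee approval as applicable. No new data are needed. The choice of level affects power: with 50 per arm and a true difference of 0, the normal approximation gives about 79% with a 95% interval and 70% with a 97.5% interval. It should be fixed before the titres are analysed by arm.

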## 3. Objectives and outcomes

We aim to include 150 adults aged 18-55 years from five Mensura EDPB sites. These will be equally randomized in two study arms receiving two doses of:

- Arm 1: 20µg BNT162b2
- Arm 2: 30µg BNT162b2

We aim to include up to 25 previously SARS-CoV-2 infected subjects per arm. The objectives of this study include assessing the immunogenicity (both humoral and cellular), safety and reactogenicity of a reduced vaccine dose.

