### **Sampling visits**

An overview of the different sample types and volumes at each study visit is summarized in table 1. Venous blood will be collected on the day of the first and second dose as well as four weeks after the second dose, and six months and one year after the first dose. Five mL of blood will be collected from all study participants at all study visits. From a random selection of 20 participants per study arm (40 in total), 36mL of heparinized blood will be collected on the day of the first dose as well as four weeks after the second dose and six months after the first dose.

The sampling activity (date, sample types collected) is documented in the eCRF. Samples are handled as detailed in the sampling manual.

One week after each vaccination dose, participants will be invited by email and text message by the research nurse to fill in a questionnaire collecting information on the reactogenicity of the vaccine.

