#### Laboratory data

Blood samples will be collected as indicated in table 1. Serum will be isolated from serum gel blood collection tubes and will be used for:

- SARS-CoV-2 specific binding antibody quantification: using an *in-house* anti-RBD IgG ELISA.
- Neutralizing antibody capacity measurement against the wild type Wuhan strain and at least one variant of concern: using a virus neutralization assay.

Peripheral Blood Mononuclear Cells (PBMC) will be isolated from heparinized blood on the day of blood draw and will be stored in liquid nitrogen for further analyses. These include:

- Memory B-cell responses: using B-cell ELISpot of flow cytometry
- T-cell responses: using intra-cellular cytokine staining

Samples will be collected at the research sites by a research nurse of Mensura EDPB.

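### The dose comparison adjusts for demographics only, although a pre-vaccination anti-RBD titre should be available for every participant and would add precision if many previously infected people enrol

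*Protocol*

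**What the plan says.** Section 3.1 defines the endpoint, taken 28 days after dose 2: "The primary outcome is the geometric mean titer (GMT) of binding (IgG) antibodies specific to the receptor binding domain (RBD) of SARS-CoV-2".

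Under Sampling visits, "Venous blood will be collected on the day of the first and second dose as well as four weeks after the second dose", with later draws at six months and one year, and "Five mL of blood will be collected from all study participants at all study visits". Table 1 agrees, with a serum tube marked at all five visits, including dose 1. Under Laboratory data, the listed uses of the serum begin with "SARS-CoV-2 specific binding antibody quantification: using an *in-house* anti-RBD IgG ELISA", with no limit by visit.

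Section 3 states: "We aim to include up to 25 previously SARS-CoV-2 infected subjects per arm". Trial randomization allocates the 150 participants without regard to infection status and stratifies on age and gender.

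Statistical analyses puts every eligible participant in the main analysis and names the method: "The level of antibody titers in each of the study arms will be analyzed with the Kruskal-Wallis test". On adjustment, that section offers just one clause: "while participant demographics (e.g. age, gender) will be taken into account (confounders". Neither the day-0 titre nor earlier infection is named as an adjusting variable. Baseline activities does have the nurse register known past infection (positive swab or serology).

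**The concern.** When up to a third of the analysis set may have met the virus before vaccination, pre-existing antibody is the obvious candidate to predict the post-vaccination titre. Nothing in the allocation or the stated analysis controls it. The sample-size section counts infection-naïve participants only, so the protocol itself treats earlier infection as relevant to this endpoint.

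Two things follow if infected and naïve participants differ after dose 2. The difference between them inflates the residual variance, which lowers power against the fixed margin of -0.15 log10. And in the one allocation that occurs, an uneven split of infected participants shifts the estimated dose difference, with nothing in the analysis to correct it. A baseline value that the trial should already hold could reduce both.

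**Working it through.** **Inputs from the protocol.** Margin 0.15 log10, SD 0.27 log10, true difference 0, two-sided 2.5% (Sample size); threshold 0.05 (Statistical analyses); 150 participants randomised equally, so n = 75 per arm, with at most 25 infected per arm (section 3).

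**Inputs assumed.** The protocol gives no difference in post-dose-2 titre between infected and naïve participants. I take d = 0.2, 0.3 and 0.4 log10, the same in both arms, with SD 0.27 within each group.

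**The plan's own figure.** n per group = 2 × [0.27 × (z + 1.282) / 0.15]². With z = 2.241 (two-sided 2.5%) this is 80.4, so 81. With z = 1.960 (two-sided 5%) it is 68.1, so 69. The stated minimum of 50 for 90% power is not reproduced; 50 per group gives 70.4% and 79.3%. That is a separate matter and does not affect the calculation below, which uses 75 per arm.

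**Power with and without the covariate.** Power = Φ(0.15 / (SD × √(2/75)) − z).

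If the infected shift is fully removed, SD = 0.27, the standard error is 0.27 × √(2/75) = 0.0441, and 0.15 / 0.0441 = 3.402. Power is Φ(3.402 − 2.241) = 87.7% at two-sided 2.5% and Φ(3.402 − 1.960) = 92.5% at two-sided 5%.

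If it is left in, SD = √(0.27² + p(1 − p)d²), where p is the infected fraction. Example: p = 25/75 and d = 0.3 give √(0.0729 + 0.0200) = 0.305.

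| Infected per arm | d (log10) | Pooled SD | Power, two-sided 2.5% (gain to 87.7%) | Power, two-sided 5% (gain to 92.5%) |
|---|---|---|---|---|
| 25 | 0.2 | 0.286 | 83.4% (4.3) | 89.5% (3.1) |
| 25 | 0.3 | 0.305 | 78.0% (9.7) | 85.4% (7.1) |
| 25 | 0.4 | 0.329 | 70.8% (16.9) | 79.7% (12.9) |
| 10 | 0.2 | 0.278 | 85.5% (2.2) | 91.0% (1.6) |
| 10 | 0.3 | 0.289 | 82.7% (5.0) | 88.9% (3.6) |
| 10 | 0.4 | 0.302 | 78.7% (9.0) | 86.0% (6.6) |

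With 5 infected per arm, the gain at two-sided 2.5% is 1.2 points at d = 0.2 and 2.7 at d = 0.3.

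**Chance imbalance.** With 50 infected among 150 and 75 drawn per arm (hypergeometric), the arms differ by 6 or more infected with probability 0.39 and by 10 or more with probability 0.12. A 30 v 20 split moves the unadjusted difference by d × 10/75, which is 0.027 / 0.040 / 0.053 log10 for d = 0.2 / 0.3 / 0.4, or 18% / 27% / 36% of the margin.

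**The case against.** **The covariate list may belong in an analysis plan.** Only the protocol is at hand, and the text does not say that demographics alone will be used. This has some force. Still, the section names the test, the analysis set and the class of adjusting variables, and a day-0 titre is not a demographic. The point concerns a stated choice that can be improved, not absent detail.

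**A reader might infer that the unadjusted result is biased.** It is not. Randomisation keeps it unbiased on average. Nor is chance imbalance a second loss of power on top of the larger variance: over repeated randomisations it is already part of the unadjusted standard error. It matters conditionally, for the allocation that occurs.

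**A reader might combine the 0.27 SD with a moderate baseline-to-outcome correlation and read off a large gain.** The protocol does not support that. It uses 0.27 in a calculation for infection-naïve participants, whose day-0 titres would be expected near the assay floor with little correlation to exploit. A useful correlation arises mainly when infected people are mixed in, and then the SD is above 0.27.

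**The table measures infected-versus-naïve separation.** This stands. Recorded infection history would capture much of the same gain. The day-0 titre would add detection and grading of unrecorded infection, and the protocol offers nothing from which to compute that increment.

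**Day-0 measurement is inferred.** This also stands. The secondary outcomes list the RBD GMT at dose 2, six months and one year, not at day 0. The inference from universal sampling and an assay list without visit limits is sound, but it is not a stated fact.

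**The stated test cannot carry a covariate.** Kruskal-Wallis has no covariate term, not even for age and gender, and gives no limit to compare with -0.15. That is a separate and more serious problem. The powers above are those of a comparison of mean log10 titres, not of the named test.

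**Conclusion.** The point holds as an improvement in precision and in protection against conditional imbalance, of uncertain size. It does not show that the planned comparison is invalid.

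At the ceiling of 25 infected per arm, a covariate that fully captures a shift of 0.2 / 0.3 / 0.4 log10 adds about 4 / 10 / 17 points of power at two-sided 2.5%, or 3 / 7 / 13 at two-sided 5%. With 10 per arm, the gains are about 2 / 5 / 9 and 2 / 4 / 7. If few infected people enrol, the gain is near zero and adjustment costs almost nothing.

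These figures rest on an assumed shift that is equal in both arms, a within-group SD of 0.27, and complete capture of the shift by the covariate. Real capture would be less than complete, so the gains are upper values for each scenario.

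**What to change.** In Statistical analyses, prespecify the following before any unblinded 28-day data are seen:

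- The primary comparison is a linear model of log10 anti-RBD IgG at 28 days after dose 2. The terms are study arm, log10 day-0 anti-RBD IgG, an indicator for a detectable day-0 titre, age and gender. Day-0 values below the assay limit are set to one fixed, stated value.
- Non-inferiority is judged by comparing the lower confidence limit of the adjusted difference (20 µg minus 30 µg) with -0.15.

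In Laboratory data, state that the day-0 sera are assayed for anti-RBD IgG in all participants.

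The cost is wording and about two degrees of freedom out of 150 participants. No additional blood draw is needed, and the assay is already among the listed uses of the serum.

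### Antibody detectability, the outcome named for the risk-factor analysis, is at its ceiling for anti-RBD IgG four weeks after dose 2; the continuous log10 titre would be informative

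*Protocol*

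**What the plan says.** The Statistical analyses section first plans a comparison of titre level between the arms by the Kruskal-Wallis test, with age and gender taken into account as confounders. It then adds a separate analysis: "Furthermore, risk factors and correlations with antibody detectability will be evaluated". P-values below 0.05 count as significant. No visit, assay or cut-off is attached to detectability.

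Every antibody outcome in sections 3.1 and 3.2 is a geometric mean titre; detectability is not among the primary or secondary outcomes. The Laboratory data section describes an in-house anti-RBD IgG ELISA and gives no detection limit.

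The only titre distribution in the protocol is in the Sample size section: "RBD-specific antibody titers (GMT, arbitrary units) 28 days after the second dose of BNT162b2 equals 2125", with a standard deviation of 0.27 on the log10 scale. The same section assumes no difference between the doses: "The true difference of GMT on log10 scale is 0".

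**The concern.** A yes/no outcome carries information about risk factors only if a reasonable number of participants fall on each side. With a typical titre of 2125 units and a narrow spread, almost nobody should fall below a detection limit four weeks after the second dose. An analysis of age, gender or any other factor at that visit would then rest on no undetectable participants, or on one. It would return nothing or an unstable estimate, and a null result would reflect the choice of outcome rather than a lack of association.

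The protocol gives this work some weight. Under Discontinuation criteria, participants who do not supply their questionnaires are withdrawn because correlation with the biological measurements would no longer be possible.

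**Working it through.** The protocol states no detectability rate or number of undetectable participants, so there is no figure of its own to reproduce. The check derives the expected number from its titre figures.

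**Inputs**
- GMT 2125, so the mean on the log10 scale is log10(2125) = 3.327 (Sample size).
- Standard deviation 0.27 on the log10 scale (Sample size).
- True difference between arms 0, so both arms share this mean (Sample size).
- 150 participants, 75 per arm (section 3).
- Non-inferiority margin 0.15 log10, used for sensitivity (Sample size).
- Cut-off c: not given, so a range is assumed.

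**Formula.** With normal log10 titres, P(undetectable) = Φ((log10 c − 3.327)/0.27), and the expected number is 150 × P.

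| Assumed cut-off (units) | log10 c | z | P(undetectable) | Expected of 150 |
|---|---|---|---|---|
| 100 | 2.000 | −4.92 | 0.0000004 | 0.00007 |
| 200 | 2.301 | −3.80 | 0.00007 | 0.01 |
| 300 | 2.477 | −3.15 | 0.0008 | 0.12 |
| 400 | 2.602 | −2.69 | 0.0036 | 0.54 |
| 450 | 2.653 | −2.50 | 0.0063 | 0.94 |
| 500 | 2.699 | −2.33 | 0.0100 | 1.5 |

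**Cut-off at which one undetectable participant is expected.** Set P = 1/150, so z = −2.475. Then log10 c = 3.327 − 2.475 × 0.27 = 2.659, and c is about 456 units, which is 456/2125 = 21% of the GMT. To expect five, the cut-off must be about 680 units.

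**How many are needed for significance.** Take a factor that splits the 150 into 75 and 75, with all undetectable participants on one side. Fisher's exact test gives p = 0.058 for five and p = 0.028 for six. At least six are therefore needed to reach the protocol's 0.05 level, even in this most favourable pattern.

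**Sensitivity at the same visit**
- Reduced-dose arm lower by the full margin (mean 3.327 − 0.15 = 3.177): among its 75 participants, 0.0005 are expected at a cut-off of 100 and 1.2 at 400.
- Standard deviation doubled to 0.54 (an assumption): 1.05 of 150 are expected at a cut-off of 100 and 4.3 at 200.

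**Other visits.** The figures above do not carry over. If the GMT were 1.0 log10 lower, at 212.5 units (an assumption, for instance late in follow-up), the expected number of 150 is 0.01 at a cut-off of 20, 1.5 at 50 and 17 at 100. Whether detectability varies there depends on a titre distribution and a cut-off that the protocol does not give.

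**The case against.** The strongest objection is that the sentence does not tie detectability to four weeks after dose 2 or to anti-RBD IgG. Serum is drawn at five visits, from the day of dose 1 to one year. Neutralising antibody is measured against wild type and at least one variant. Up to 25 participants per arm may have been infected before, so detectability should vary before dose 1. A reader might infer that the planned analysis cannot identify any risk factor at all. The protocol does not support that: its titre figures cover one assay at one visit, and at a GMT 1.0 log10 lower there could be a usable number of undetectable participants. This part of the objection stands and limits the point. Variation before dose 1 helps little, however, since it would mainly mark earlier infection, which is already recorded at baseline, rather than response to vaccine.

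Second, no detection limit is given, so the result does not follow from the protocol's figures alone. This also stands. But the conclusion at four weeks is the same for every cut-off up to about 450 units.

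Third, titre level is already analysed in the preceding sentence of the section. That is true, but that sentence compares the arms and treats age and gender as confounders; it does not evaluate them as risk factors.

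Fourth, this is one exploratory sentence, and a statistical analysis plan that is not shown may settle the visit, cut-off and model. Their absence is indeed no fault. The outcome, however, is a choice that the protocol states, and an analysis plan that follows the protocol would inherit it.

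**Conclusion.** The point holds for anti-RBD IgG four weeks after dose 2. There the protocol's GMT and standard deviation imply fewer than about 1 undetectable participant of 150 for any cut-off up to about 450 units, against at least six needed for significance in an even split. At that visit the binary outcome is at its ceiling and uninformative about risk factors.

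This rests on log10 titres being roughly normal, on the stated GMT and standard deviation applying to all 150 participants including those previously infected, and on a cut-off within the assumed range. A much wider spread combined with a high cut-off would weaken it.

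No such conclusion is drawn for the other visits or for neutralising antibody. What can be said there is only that reducing a quantified titre to detectable or not discards information. The analysis is exploratory and has no part in the non-inferiority conclusion, so this is an improvement at no cost rather than a defect in the main result.

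**What to change.** In the Statistical analyses section, replace antibody detectability as the outcome for risk factors and correlations with the log10 anti-RBD IgG titre, treated as continuous, at four weeks after dose 2 and at the other post-dose visits (day of dose 2, six months and one year after dose 1). Report detectability only as a descriptive percentage per visit.

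The cost is one sentence. The same assay results are used, and no extra samples, visits or participants are needed.
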